## **1. BACKGROUND AND RATIONALE**

Annually, approximately 80-100 patients within NNI and TTSH public hospitals with severe stroke, traumatic brain injury (TBI) and spontaneous subarachnoid haemorrhage (SAH) undergo unilateral or bilateral wide decompressive craniectomy (DC) due to raised intracranial pressures. Such life-saving surgeries leave survivors with a sunken skull bone flap in the recovery phase. Following subacute inpatient rehabilitation, ~50%-75% of patients regain locomotor abilities and are ambulant with varying degrees of assistive aid. Upon discharge, most are able to further improve to supervision or modified independence functional mobility levels in the community.

As a result of residual stroke or TBI related residual motor, balance and / or sensory weakness, cognitive and behavioral impairments, impulsivity, these patients are identified to have significantly increased fall risk. Furthermore, the unprotected cerebrum post DC is particularly vulnerable to secondary injury from minor falls, in addition to long-term post DC complications such as flap herniation through the bony skull defect, hydrocephalous and syndrome of the trephined brain. Definitive elective cranioplasty either with artificial materials or autologous bone flap provides the only solution to these poorly understood conditions.

An average 3 -6 months' interval from acute craniectomy to definitive cranioplasty is common due to several factors. These include time needed for spontaneous neurological recovery, resolution of acute neurosurgical and medical complications, healing of the craniectomy wound and completion of inpatient rehabilitation (mean rehabilitation length of stay @TTSH Rehabilitation Centre ~30 days). Other factors include individual neurosurgeons' practice, patient/family consent, implant selection and fabrication time.

During this period, there is no protection for the skull defect. While general guidelines agree that helmet wear is mandatory from the early phase of recovery and during ambulation to protect the skull flap, there is no agreed protocol for post DC cranial defect management and often poor compliance to protective helmets exists. Standard measures include off the shelf bicycle or riding helmets (\$30-\$40 each) or ventilated and rigid head protection helmets (~\$300-500 each), are uncomfortable in Singapore's tropical climate and need to be individually imported. The latter are currently used at TTSH Rehabilitation Centre for mobile patients undergoing ambulation training or who are independent. However, they are hot in our tropical weather, heavy, uncomfortable and are socially not acceptable with poor cosmesis to recovering patients who may have physical and functional impairments, hence compliance is extremely low and the large majority of patients awaiting elective cranioplasty are observed wearing caps, hats or head scarves rather than head protection helmets in the post-discharge phase while awaiting cranioplasty.

While the AHA/ASA concludes that DC is a life-saving procedure, little is written in the literature about the optimal care management of the skull defect in the post DC phase. (Livesay S 2011)

### **1.1. General Introduction**

Decompressive Craniectomy (DC) is a surgical procedure that involves removing a portion of the skull and closing the scalp without reimplantation of the bone, commonly as a life-saving surgery after

malignant cerebral infarctions, intracerebral hemorrhages and severe traumatic brain injury. This results in a cranial defect. Craniectomy helps to increase the buffering capacity of the cranium, allows outward herniation of brain tissue and reduces intracranial pressure. (Mayfieldclinic.com/PE-TBI.htm) ([www.jpma.org.pk/full\\_article\\_text.php?article\\_id=3932](http://www.jpma.org.pk/full_article_text.php?article_id=3932))

Though the procedure is technically straightforward, serious complications, apart from wound infections, have been reported in the acute and chronic phase. These include herniation of the cerebral cortex through bone defect, subdural effusion, seizures, hydrocephalus and syndrome of the trephined. About half of the patients in a study by Honeybul et al in 2011, had at least one complication following craniectomy. It was found that the presence of at least one complication significantly doubled the length of stay in the hospital or rehabilitation facility. (<https://doi.org/10.1089/neu.2010.1612>).

In a literature review of more than 60 publications, patients post DC, were identified to be high fall risk and at high risk of injury. Fall prevention and protection of exposed cranium from fall or pressure were considered important in the first few weeks post craniectomy. (Livesay S 2014).

Post DC patients are deemed to be lacking optimal coordination and balance and run the risk of trauma to the unprotected brain should they fall (Bostrom S, 2005).

In a separate study, it was recommended that post craniectomy patients should be considered high risk and institutions should establish or review their current management guidelines. (Honeybul S 2009). It was also recommended that falls risk assessment be done in this group of patients and helmet use be made mandatory in rehabilitative exercises (Bostrom S 2005)

Despite this, secondary traumatic brain injury following DC has rarely been reported. A solitary case report from a Perth hospital) documented a post-DC well-recovering patient after initial head trauma who suffered a fall on the bony defect and subsequently died from this secondary cerebral trauma. This underpins the importance of adequate preventive head protection for all DC patients. (Honeybul S 2009)

## **1.2. Rationale and justification for the Study**

Currently, there exists no locally produced, viable, customized-skull defect protective external prostheses that is available to post DC patients in the recovery phase. A recently launched overseas prototype is referenced. ([www.anatomics.com](http://www.anatomics.com))

A proof-of-concept (POC) proposal to study the feasibility of customized head protection prototype device (HPPD) using 3D printed externally-applied prostheses integrated to the craniectomy bony skull defect. The proposed material is a bio-compatible, light-weight rigid /semi rigid material which can be fitted to the skull defect and interfaced with the subject's bony rim using soft, deformable material (e.g. silicon) and attached using an elastic head band. The prosthesis is removable for skin/prosthesis cleansing.

Our hypothesis is that the fabricated HPPD will be fitted feasibly and undergo a proof of concept trial for safety and wearability with systematic monitoring.

### **a. Rationale for the Study Purpose**

There has to date, been only 1 publication concerning a novel method described by S. Bostrom (2005)

et al in a Swedish hospital where the doctors used methyl metacrylate (a type of bone cement in joint replacement surgery) to form an acrylic flap to cover the whole craniectomy site. The flap was created immediately post craniectomy, and was roughly up-sized to 12x13 centimetres to cover the bony defect and fixed to the skull with microplates temporarily until final cranioplasty was achieved with the patient's own bone flap. However, this procedure necessitated the creation of a larger skin dissection to cover the enlarged acrylic flap and prolonged the operation time by 40 minutes. In this study, 4 patients successfully underwent this temporary invasive procedure. Though this method attempted to address the shortcomings of helmet wearing, it was invasive, not fully customised and carried with it, the risks of prolonged surgical and anaesthetic times. (Bostrom 2005)

Though mandatory helmet use post DC has been recommended during rehabilitation exercises, the uptake is low in the local rehabilitation setting. (Bostrom S 2005) The common reasons given by patients are discomfort of helmet use in the local tropical climate, high cost of a rigid protective appropriate- sized helmet given the relatively short time prior to cranioplasty and poor aesthetic appeal and social acceptability of the helmet. For off-the-shelf helmets, the situation is similar and an optimal fit and contour may not be possible

Hence, this necessitates a lighter, aesthetically appealing protective head protection device for a post DC patient in order to prevent secondary brain injury in the event of a fall during the recovery phase.

Hence, our study hopes to craft a lightweight non-invasive external prosthesis that is customised to the defect's size. The customised head protection prototype device (HPPD) is thus proposed with the added benefit of being detachable for hygiene purposes.

**b. Rationale for Doses Selected**

Not applicable

**c. Rationale for Study Population**

Subjects with acute or chronic skull defects as a result of surgical decompressive craniectomy (DC) who have refused, are not medically fit or are waiting for definitive cranioplasty.

**d. Rationale for Study Design**

As this is a first time in human study, the study design is exploratory open label pilot study with independent assessor.

**2. HYPOTHESIS AND OBJECTIVES**

The objectives of this exploratory feasibility study are to test for the first time in human, customized 3D printed fabricated prostheses by additive manufacturing using biocompatible materials in suitable subjects with a post decompressive craniectomy skull defect.

## **2.1. Hypothesis**

Our primary hypothesis is that 80% of subjects will be safely fitted with head protection prototype devices (HPPD) without immediate complaints of pain or discomfort or signs of bony defect scar pressure or redness or wound breakdown within the first 2 hours in the research clinic.

Our secondary hypothesis is that 70% of these subjects will be without complaints of pain or discomfort or signs of bony defect scar pressure or redness or wound breakdown in the first week of outpatient monitoring.

In addition, subjects will tolerate HPPD wear progressively up to 8 weeks for specified high risk activities.

We anticipate a 25% dropout rate at 8 weeks.

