## **6. METHODS AND ASSESSMENTS**

1. Proof of Concept with open label pilot feasibility clinical trial.
2. Number of subjects to enrol: 10 (5 to 9 from TTSH and 1 to 5 from NNI)
3. Outpatient monitoring phase for up to 8 weeks (1 screening, 1 fitting, 4 follow up visits and 3 phone visits]
4. If planned cranioplasty is performed within 8 weeks of study inclusion, subject involvement will end on date of scheduled cranioplasty.
5. Assessments involve subjective evaluation of suitability of fit and complications during visits, patient and NOK log of duration of wearing and subjective complaints.
6. Digital photographs with pixilation of facial features or short video clips to document fit or outcome will be taken if subject consents. These may be used for education or safety review of the investigational product

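### The week-1 success criterion has no wear condition, so a fitted subject who silently leaves the device unused at home counts as a success

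*Protocol*

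**What the plan says.** Protocol section 2.1 gives two numerical targets. The primary one concerns the clinic: "Our primary hypothesis is that 80% of subjects will be safely fitted with head protection prototype devices (HPPD) without immediate complaints", judged over the first 2 hours. The secondary one concerns home use: "70% of these subjects will be without complaints of pain or discomfort or signs of bony defect scar pressure", continuing "or redness or wound breakdown in the first week of outpatient monitoring". The sentence ends there, with no minimum wear time, number of wear days or adherence to a schedule. A separate sentence says that "subjects will tolerate HPPD wear progressively up to 8 weeks for specified high risk activities", without a threshold.

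Wear appears in other places:
- Section 1 (Background) says of the helmets now in use that "compliance is extremely low".
- Section 2.2 lists compliance among the things to be monitored under the third primary objective.
- Section 2.4a names usability, together with lack of complications, in the efficacy endpoint.
- Section 6, item 5 plans a "patient and NOK log of duration of wearing and subjective complaints".
- Section 6.3 has the subject take the device home after Visit 1 with a progressive wearing schedule and monitoring logs.

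None of these is linked to the 70% target or carries a threshold of its own.

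**The concern.** The 70% figure is meant to show that the device is tolerated at home. A criterion made up only of absent complaints and signs can be met in two ways: by wearing the device without trouble, or by not wearing it. The protocol does not separate them. An unworn device cannot cause pain, scar pressure, redness or breakdown, so poorer compliance improves the result.

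The trial's own rationale is that patients do not wear the head protection now available, so non-wear cannot be dismissed. What is at stake is how the pilot is read: section 2.3 makes wider multi-centre use depend on success here. A week-1 rate that mixes tolerance with non-use could be quoted in support of a device that was little worn.

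**Working it through.** The protocol derives no figure for this target. Section 11.1 states that no detailed sample size calculation was made, so there is nothing to reproduce. The check has two parts.

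**1. Reading the criterion.** Consider a subject fitted at Visit 1 who does not wear the device at home and reports nothing. Such a subject has no device-related complaint and no device-related sign in week 1, and so meets every condition in section 2.1.

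**2. Size of the effect.**

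Inputs from the protocol: n = 10 (sections 3.1 and 11.1) and the 70% target (section 2.1), hence 0.70 × 10 = 7 successes needed.

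Assumptions, not in the protocol:
- m subjects do not wear the device at home, and all m count as successes.
- Each of the other n − m subjects is free of complaints and signs with probability p, independently.

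Formulas:
- Expected apparent success rate = [m + (n − m) × p] / n
- Chance of meeting the target = P(X ≥ 7 − m), where X is binomial (n − m, p)

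For p = 0.50:
- m = 0: rate 5/10 = 50%; P(X ≥ 7 of 10) = 176/1024 = 0.17
- m = 2: rate (2 + 4)/10 = 60%; P(X ≥ 5 of 8) = 93/256 = 0.36
- m = 4: rate (4 + 3)/10 = 70%; P(X ≥ 3 of 6) = 42/64 = 0.66
- m = 5: rate (5 + 2.5)/10 = 75%; P(X ≥ 2 of 5) = 26/32 = 0.81

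Chance of reaching 7 of 10 over a range of p:

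| p among wearers | m = 0 | m = 2 | m = 4 | m = 5 |
|---|---|---|---|---|
| 0.30 | 0.01 | 0.06 | 0.26 | 0.47 |
| 0.50 | 0.17 | 0.36 | 0.66 | 0.81 |
| 0.70 | 0.65 | 0.81 | 0.93 | 0.97 |

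The secondary target refers back to subjects already mentioned and may mean only those fitted successfully. If that is 80% of 10 = 8 subjects, then 0.70 × 8 = 5.6, so 6 successes are needed. With p = 0.50 the chances are 0.145, 0.344, 0.688 and 0.875 for m = 0, 2, 4 and 5. The pattern is the same.

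**3. With a wear condition.** Take n = 10 and m = 4. As the criterion stands, the four non-wearers count and only 3 of the 6 wearers need be free of complaints. If success also requires wear and all 10 stay in the denominator, the most that can be reached is 6/10 = 60%, below the target. If the rate is instead taken among wearers, its expected value is p, whatever m is.

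**The case against.** The case on the other side has force on several points.

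**Non-use as the most likely behaviour.** A reader might infer this from the helmet experience. The documents do not support it. The low compliance concerns helmets described as hot, heavy and cosmetically poor, and this device is designed to avoid those faults. Inclusion criterion 9 asks for a relative who supervises donning and monitors compliance, with self-monitoring allowed under exclusion criterion 9. Exclusion criterion 5 removes subjects whose behavioural, mood or addiction problems would impair compliance. Subjects also receive education and a wearing schedule. Non-use is realistic; no more than that can be said.

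**Stopping for discomfort scored as a later success.** This too might be inferred, and it fails. A subject who reports discomfort in week 1 has already failed the criterion. Reports are sought early, by telephone on day 1, again three days later, and at Visit 2. After week 1 there is no proportion to be met, because the 8-week sentence has no threshold. The gap is confined to subjects who do not wear the device and report nothing.

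**A log that records duration only.** Section 6 describes the log in one line. The log form is not shown, nor are the questionnaires listed as Appendix 3. Whether wear during high-risk activities is recorded cannot be judged, so no addition to the log is requested.

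**Low use would be visible anyway.** Compliance is monitored under a primary objective, so it could be seen beside the week-1 rate. That is a fair mitigation, but the 70% claim itself would still be scored without regard to wear.

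**A composite blurs safety, and the detail belongs in an analysis plan.** Mixing adherence with skin findings can hide a safety signal, and the fix therefore keeps a separate rate among wearers. An analysis plan that is not shown might add a wear condition, but the protocol itself fixes the target and the definition of success without one.

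**Conclusion.** The point holds in this form: the week-1 target omits wear, silent non-wearers count as successes, and more non-wear makes the target easier to meet. In the illustration with p = 0.50, four non-wearers among 10 raise the chance of meeting it from 0.17 to 0.66 with no change in how well wearers tolerate the device.

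The number of non-wearers and p are assumptions, and the documents give no figure for either. The direction does not depend on their values. It needs only that non-wearers are free of complaints and signs more often than wearers.

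The 2-hour primary criterion is not affected, since the device is fitted and observed in the clinic. In an exploratory pilot of 10 subjects the defect does not undermine the study, but it biases the only numerical outpatient result towards success. It should be corrected.

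**What to change.** Amend the secondary hypothesis in section 2.1, using the wear log already planned in section 6, item 5:

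- Define week-1 success as logged home wear in line with the wearing schedule issued at Visit 1 **and** no complaint or sign in that week. The investigators set what counts as in line with the schedule.
- Do not count non-wearers as successes. Say whether they stay in the denominator or are shown separately, and how a missing log is treated.
- Count stopping wear because of the device as a failure.
- Report the complaint and sign rate among actual wearers, with the logged wear beside it, so that the safety signal stays separate from adherence.
- State whether the 70% applies to all enrolled subjects or to those fitted.

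The cost is wording only, with no extra visits or data collection. The downside is a possibly lower success rate or, for the rate among wearers, a smaller denominator in a trial that has only 10 subjects.

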## **2.2. Primary Objectives**

These are to (1) test the feasibility and safety of customised 3D printed HPPD, (2) integrate the prostheses to the skull defect in removable manner and discharge patient with appropriate education, (3) to systematically monitor subjects for symptoms, compliance, complications and subjective feedback during the outpatient phase where progressive wear of HPPD and monitoring of acceptability will be monitored.

## **2.3. Secondary Objectives**

As the grant duration is a short 12 months, secondary objectives will not be hypotheses-driven.

These may include more widespread multi-centre use of the HPPD if proven successful in this pilot and serve as a prototype for further improvement and development as a new collaborative service incorporating the HPPD occurring early after craniectomy.

## **2.4. Potential Risks and benefits:**

### **a. End Points - Efficacy**

Successful fabrication and integration of HPPD and feasibility of clinical use by subjects in terms of usability and lack of complications.

### **b. End Points - Safety**

These include:

- (i) Unable to fit subject safely with regards to wounds.
- (ii) Failure to fabricate a usable or safe HPPD.
- (iii) Skin allergy or reaction or pressure related complications to the HPPD or attachment straps

## **3. STUDY POPULATION**

### **3.1. List the number of subjects to be enrolled.**

Number of subjects to enroll: 10 (5 to 9 from TTSH and 1 to 5 from NNI)

Study subjects will be drawn from inpatient ward admissions from NNI and TTSH Rehabilitation Centre wards and TTSH rehabilitation outpatient clinics @AMKH and TTSH CART 5B via face to face contact. Permission will be obtained from primary physicians.

### **3.2. Criteria for Recruitment**

Clinical assessment for eligibility will follow strict adherence to the screening protocol. Study team will determine suitability for recruitment based on the following criteria. There are no subject recruitment restrictions based on age, gender or race.

### **3.3. Inclusion Criteria**

All subjects must meet all of the inclusion criteria to participate in this study.

1. Age 21 to 80 years, both males and females.
2. Presence of surgical unilateral or bilateral craniectomy performed for reasons of ischaemic or haemorrhagic stroke, Subarachnoid haemorrhage (SAH), traumatic brain injury (TBI), benign cerebral tumours, etc.
3. Stroke, SAH or TBI are diagnosed by specialists and confirmed on brain imaging studies (CT, MRI)
4. Duration from event > 30 days and either during inpatient or outpatient phase.
5. Presence of at least 1 post decompressive craniectomy CT brain film performed at NNI/TTSH.
6. Healed craniectomy surgical wound without bulging skin flap or active skin infection.
7. Patients awaiting elective cranioplasty or those who refuse cranioplasty.
8. Ability to understand simple instructions.
9. Presence of family members or NOK who can supervise the patient to don the head protection device, care for the material and regularly monitor for compliance and complications.
10. Reproductive age females should not be pregnant at the point of consent-taking and during the study.

#### *Exclusion Criteria*

All subjects meeting any of the exclusion criteria at baseline will be excluded from participation.

1. Patient in vegetative or minimally responsive state.
2. Presence of uncontrolled medical condition (uncontrolled hypertension, Diabetes Mellitus, sepsis or delirium, active malignancy either cranial or extracranial sites)
3. Presence of end organ failure (end stage renal or liver failure, renal dialysis, life expectancy <6 months)
4. Presence of pregnancy or lactation.
5. Presence of severe agitation /behavioural/active depression or anxiety/ drug or alcohol addiction which would negatively affect compliance,
6. Presence of unhealed head wound, active wound infection, scalp dermatitis, wound breakdown which would be worsened by pressure from the HPPD.
7. Presence of known allergy to the investigational products which is the 3D printed material (e.g. Nylon).
8. Subjects' CT brain imaging films are not available to the study team.

9. Absence of NOK who can assist monitoring unless subject is able to self-monitor.

### **3.4. Withdrawal Criteria**

Reasons for discontinuation of study intervention/product:

1. Completion of all study interventions and visits.
2. Failure to fit suitable HPPD.
3. Development of allergic reactions deemed due to the HPPD.
4. Development of new surgical scar infection deemed related or unrelated to the HPPD.
5. Unrelated medical or neurosurgical complications which alter eligibility to participate in the study.
6. Failure of study sponsor or vendor providing HPPD.
7. Study closure due to DSMB review.

